### 3 TRIAL DESIGN

A two-arm, cluster randomisation trial of portable HEPA air filters versus no air filters for reducing symptomatic winter respiratory infections (including COVID-19) in care home residents with mixed method process and economic evaluation.

#### 3.1 Project timetable

The funding start date for this trial is 01 July 2021 and the study duration is expected to be 42 months, to 31st December 2024 (subject to change).

#### 3.2 Internal pilot

Following set-up, we will carry out a nested internal pilot study for up to six months (winter 1 will end 31 May, assuming COVID-19 is still prevalent). We aim to confirm care home and resident recruitment, follow up and event rates, the intervention is being used as intended and assess unintended consequences. Detailed information will be gathered during the internal pilot from both the qualitative and quantitative elements of the study to inform optimisation and refinement of study processes; and stop/go progression criteria (Table 2 below).

**Table 2. Progression criteria, stop/go with a traffic light progress**

| Criterion (planned number by end of winter 1 – 31 May)                                                                 | Stop/go progression criteria                                               |                                                                                     |                                                                            |
|------------------------------------------------------------------------------------------------------------------------|----------------------------------------------------------------------------|-------------------------------------------------------------------------------------|----------------------------------------------------------------------------|
|                                                                                                                        | Traffic Light Progression                                                  |                                                                                     |                                                                            |
|                                                                                                                        | Stop (if any of):                                                          | Amend (if any of):                                                                  | Go (if all of):                                                            |
| Care home consented to use of air filters in communal rooms.                                                           | ≤5 care homes consented                                                    | 6-7 care homes consented                                                            | ≥8 care homes consented                                                    |
| Mean of intervention care home residents consented to have air filter in private bedroom .                             | <5 residents consented per care home                                       | 5-7 residents consented per care home                                               | >7 residents consented per care home                                       |
| Communal, staff-only, and private bedroom air filters sited as intended and not switched off for a mean of the checks. | <40% of checks                                                             | 40-50% of checks                                                                    | >50% of checks                                                             |
| Communal, staff-only, and private bedroom air filters cleaned, and air filter replacement for a mean of the checks.    | <30% of checks                                                             | 30-50% of checks                                                                    | >50% of checks                                                             |
| Primary outcome data collection (days)                                                                                 | <4652 resident days complete data for main comparison primary outcome      | ≥4652 and <5351 resident days complete data for main comparison primary outcome     | ≥5351 resident days complete data for main comparison primary              |
| Primary outcome data collection (proportion)                                                                           | <70% follow up days complete for primary outcome among consented residents | ≥70% and <80% follow up days complete for primary outcome among consented residents | ≥80% follow up days complete for primary outcome among consented residents |

#### 3.3 Planned recruitment

A total of 91 care homes will be recruited for AFRI-c, with a mean cluster size of 12 consented at the start of the winter period. We anticipate recruiting at least 1002 consented participants throughout the course of the study to allow for drop out and the model of continuous recruitment. Further details about the trial setting are provided in the next section (Section 4). Recruitment is seasonal, therefore each care home will only be involved for 1 winter season. The duration of recruitment will be over 3 winters. In our recruitment progression estimates, we assumed that 10 care homes noted in Section 3.2 would be set-up and recruiting by month 6 of the internal pilot phase.

### **3.4 Taking account of the SARS-CoV-2 pandemic**

The trial was designed anticipating the SARS-CoV-2 pandemic would remain active for at least the first study year. Since care home managers advised that access for research staff to care homes may be restricted for the foreseeable future, it was concluded that a 'remote' data collection policy was required, with research staff supporting study activities with telephone and video communications. The main risk of this approach is that staff will be too busy with care home responsibilities to assist with study activities.

To minimise this, we have decided: (i) to select care homes with that are the most engaged in the study with varying levels of research experience, e.g. via the NIHR ENRICH network; (ii) to request care homes provide the study team with anonymised data such that consent is necessary only for air filters to be installed, and for medical notes review; (iii) consent will be overseen by CRN/ study researcher experienced and trained in the enrolment and retention of older people with and without capacity to consent; (iv) all data will be collected by care home staff (i.e. not relying on residents to grapple with website forms) using simple-to-use forms collecting the minimum, necessary data; (v) to appoint 'care manager study champions' to ensure smooth running of study processes and data completion, and be points of contact; and (vi) to provide the care homes with financial reimbursement.

#### **4 TRIAL SETTING**

This trial will be delivered through care homes providing personal, with/without nursing, with/without dementia care to people predominantly over the age of 65 years in the UK. We will approach NIHR ENRICH Research Ready Care Home Network. Additional care homes will be identified via other routes, if required. Where possible, care homes will be selected to facilitate: (i) maximum NIHR CRN nurse support; and (ii) geographically clustered to facilitate the study researcher visits.

## 5 ELIGIBILITY CRITERIA

### 5.1 Participant population

Adults residing in a care home in the England.

### 5.2 Care homes

#### 5.2.1 Inclusion criteria

- Capacity for  $\geq 20$  residents residing in single bedrooms\*
- Care homes which predominantly focuses on care for older people (residential home/nursing home)
- Willing to maintain a register of all residents, to be updated weekly until the end of April, after which new residents will not be invited
- Willing to invite residents to receive air filters and/or accept medical notes review until average of 12 (maximum 16) agree (the “consented”) per care home
- Willing to provide anonymised resident infection data, administer brief resident and staff questionnaires, and respond to data queries
- Care home owner permission to take part in study
- Willing to commit to installing air filters in care home if allocated to the intervention group
- Willing to commit to not installing air filters if allocated to control group

#### 5.2.2 Exclusion criteria

- CQC website rates as ‘inadequate’ or ‘requiring improvements’
- $\geq 10\%$  private bedroom use of portable HEPA filtration devices
- Participating in a competing\*\* care home level study

**\*single bedrooms:** residents residing in a room of single occupancy will be referred to as residents in a private and/or single bedroom. Residents may share bathroom facilities.

**\*\*Competing studies:** Competing studies are those whose aim (or a plausible consequence) is to prevent infections or reduce infection severity. Co-enrolment in the AFRI-c study and another competing study should be avoided due to potential impact on the study objectives and resident burden and safety.

### 5.3 All residents

#### 5.3.1 Inclusion criteria

- Expected to reside in the care home for at least 1 month of the care home data collection period

#### 5.3.2 Exclusion criteria

- Terminal illness (death expected within seven days)

We recognise that it will take more time and effort to proactively enrol residents who are more vulnerable. It is imperative however that active steps should be taken TO ENROLL the following groups of residents wherever possible. Those:

- With extreme age e.g.  $>90$  years of age and/ or advanced frailty
- Who are bed-bound
- Who are usually semiconscious or unconscious, or whose conscious levels vary
- Who have a diagnosis of dementia, or have cognitive impairment

## **5.4 The “consented” residents**

The following eligibility criteria are for the “consented” residents invited to receive an air filter and/or permit medical notes review **only**:

### **5.4.1 Inclusion criteria**

- In single occupancy bedroom
- Expected to reside in the care home for at least 1 month of the care home data collection period
- Able to give informed consent (or if lacks capacity, a consultee is willing to complete a consultee declaration form)

### **5.4.2 Exclusion criteria**

- Participating in any interventional\* study
- Terminal illness (death expected within seven days)

### **5.4.3 Co-enrolment in other research studies**

\*Interventional study: Interventional studies are those which involve an ‘intervention’. In medical terms this could be a drug treatment, surgical procedure, diagnostic test or psychological therapy. Examples of public health interventions could include action to help someone to be physically active or to eat a more healthy diet. Examples of social care interventions could include safeguarding or support for carers. If a site becomes aware that a participant has enrolled in an interventional study whilst taking part in AFRI-c, they should inform the central research team (UoB). The research team will evaluate whether it is appropriate for the resident to continue participating in AFRI-c.

## 6 TRIAL PROCEDURES

Approximately 91 care homes will be recruited and randomised (enrolled) over a 22-month period. This section outlines the key trial procedures from identification of potential care homes (section 6.3 and 6.4) and residents (section 6.5) through to end of the trial. An overview of the trial is shown in a flow diagram on page 9. An overview of key time points are depicted in the flow diagram below on page 25.

### 6.1 Schedule of trial assessments and outcomes (overview)

Table 3, below, details the key assessments/outcome measures along with care home and participant-related procedures scheduled at various trial timepoints. The care home data collection period will be the winter months (usually defined as 1 September to 31 May assuming COVID-19 is still prevalent) during which the air filters will be switched on and anonymised infection data collected daily from all eligible residents that do not opt-out of study involvement.

To summarise, the following research activity will take place:

1. Care homes will be identified and screened
2. Care homes will sign up to take part in the trial and be randomised
3. Eligible residents will contribute baseline and follow-up data on a daily basis over the winter period (capped at approx 30 randomly selected residents for winters 2 & 3)
4. Care home staff will be invited to complete baseline and follow up questionnaires on an optional basis
5. Some care home staff, residents/consultees and residents' relatives will be invited to take part in a qualitative interview

A subgroup of residents (average of 12, maximum of 16 per care home) will be selected at random to be consented to provide permission to access medical records. In intervention care homes, these "consented" residents will also be invited to receive air filters in their private bedroom. The consent process for these residents will be detailed in section 7.

## 6.2 KEY TIME POINTS FLOW CHART

[figure not shown]

\* Replacement residents may be consented throughout the care home data collection period. Residents are eligible if expected to reside in care home  $\geq 1$  month during the care home data collection period and if willing to accept same units with new air filters.

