#### **6.4.5 Randomisation and allocation specific training**

Following green light activation, and baseline data being received, the care homes will be randomised to receive either the intervention (usual care plus HEPA filters) or control (usual care) (see section 10 and 11). Randomisation will be stratified by whether they provide nursing care yes/no; and socioeconomic tertile (high/medium/low)) using a randomisation list pre-generated by a CTU statistician with no other involvement in recruitment activities.

Following randomisation, care homes will be informed of their allocation.

Intervention care homes will complete additional study training, specific to the use of devices in their care homes – e.g. installation, monitoring and maintaining air filters (according to manufacturer instructions), recording of outcomes and the arrangements for delivery of the air filters to the relevant care homes. For care homes allocated to the intervention, training will also involve discussions of where to locate communal room air filters. Staff will then begin inviting an average of 12 (maximum of 16) residents per care home to participate to receive an air filter in their private bedrooms and/or provide access to their medical records (see section 6.5) and share identifiers with the UKHSA.

In the control care homes staff will begin inviting an average of 12 (maximum of 16) residents per care home to participate provide access to their medical records (see section 6.5) and share identifiers with the UKHSA.

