### **6.15.2 Resident change in participation status**

Consented residents can request to change their participation status in the study at any time. They can change their participation by requesting to stop any of the following:

- i) Having an air filter in their private bedroom (intervention residents only)
- ii) Access to their medical records

Even if a resident decides to change their participation by no longer having an air filter in their bedroom or allowing access to their medical records, they can still contribute data to the daily anonymised data collection elements (unless they opt-out of this).

If a consented resident changes their participation in the study between the period 1st Sept to 1st May, a replacement resident will be sought following the procedures in sections in section 6.5; consent to join trial, baseline data collection and follow up. If a resident in the intervention group decides they no longer want an air filter in their private bedroom, the newly consented resident will be offered the same shell air filter unit but the study will supply a new inner air filter. Used air filters may be sent to the laboratory for storage as detailed in section 10.7.

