Based on 90% power and an alpha of 0.05, to detect a reduction in winter respiratory infections of 1 per 242 person days from 2 to 1 per 242 person days, assuming a coefficient of variation of 0.78 to allow for between care home infection rate variation, calculated from data provided in personal communication from the PRINCESS study team,(34) a total of 74 care homes will be required. This assumes a mean cluster size of 12 for winter 3 (10 participants per care home for winters 1 & 2) and accounting for an attrition level as observed in PRINCESS,(34) and the continual recruitment strategy as described above, each cluster will provide a mean of 1920 person days of follow up. After reviewing accumulating data with the DMC and TSC on the number of follow up days, a decision was made to increase the number of care homes taking part in Winter 3 from 32 to 46 in order to achieve the number of person days required in the original calculation. This gives an approximate total of 91 care homes taking part in the study overall.

Each care home will participate for a single winter season (usually 1 Sept to 31 May). We estimate that 10 care homes will be randomised in winter 1 (the most experienced) and then 35 in winter 2 and 46 in Winter 3.

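### The flow-chart footnote makes accepting the re-used filter a condition of eligibility for replacement residents, contrary to 5.4.1 and 6.15.2; if followed, entry to the primary analysis set differs by arm after randomisation

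*Protocol*

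**What the plan says.** The 6.2 footnote allows replacement residents to be consented throughout data collection. They are eligible if expected to stay at least one month and "if willing to accept same units with new air filters".

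Other sections describe entry to the consented group differently:

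- **5.4.1** has three criteria: a single-occupancy bedroom, the one-month expected stay, and "Able to give informed consent (or if lacks capacity, a consultee is willing to complete a consultee declaration form"). None concerns the filter, and 5.4.2 adds no filter-related exclusion. Neither section separates initial from replacement residents.
- **5.2.1** describes the home's undertaking as "Willing to invite residents to receive air filters and/or accept medical notes review". Section **6.4.5** has intervention homes inviting residents "to receive an air filter in their private bedrooms and/or provide access to their medical records". The opening of 5.4 and section 6.5.1 use the same and/or construction.
- **6.15.2** sends sites back to 6.5 for replacements. Where a resident has given up a filter, it says that "the newly consented resident will be offered the same shell air filter unit", with a new inner filter.
- **6.6** states that consented residents in the intervention arm will get a filter for the winter.

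The primary analysis (13.1.2) is by intention to treat on the consented residents.

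**The concern.** Homes know their allocation before residents are approached (6.4.5), and sites work down a random list when someone declines (6.5.1). Take a listed replacement who would agree to notes review but not to a bedroom filter. A control home enrols that person. An intervention home following the footnote passes over them to the next name. Willingness to take the treatment then becomes an entry criterion for the primary set, applied after randomisation and in one arm only, and the random list no longer protects comparability for those residents.

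Section 6.15.2 adds a route that exists only in intervention homes. A resident may stop having the filter, and a change in participation between 1 September and 1 May triggers a search for a replacement. Giving up a filter can therefore open a place that, under the footnote, only someone willing to have one may fill.

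If acceptors and decliners differ in their underlying infection rate or in how symptoms are noticed, the arms would differ for reasons other than the filters. The protocol has no data on whether they do.

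**Working it through.** **1. The plan's own figure.** Inputs from 13.1.1: "Based on 90% power and an alpha of 0.05"; a fall "from 2 to 1 per 242 person days"; "assuming a coefficient of variation of 0.78"; 1920 person-days per home. Two-sided alpha is assumed. The cluster formula for rates is

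c = 1 + (z₀.₉₇₅ + z₀.₉₀)² × [(r₀ + r₁)/y + k²(r₀² + r₁²)] / (r₀ − r₁)²

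With r₀ = 2/242, r₁ = 1/242, y = 1920 and k = 0.78, c = 36.94. That rounds up to 37 per arm, 74 homes in total, as stated. The sample size does not depend on this point. The calculation matters here only for the planned rate ratio, 1/2 = 0.5.

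**2. The sections side by side: is a filter required?**

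| Section | Initial intervention resident | Replacement intervention resident | Control resident |
|---|---|---|---|
| 5.4.1, 5.4.2 | no | no | no |
| 5.2.1, 6.4.5, 6.5.1 | no (and/or) | no (6.15.2 refers back to 6.5) | not applicable |
| 6.15.2 | not addressed | no (offered) | not applicable |
| 6.2 footnote | not addressed | yes | cannot apply |
| 6.6 | implied yes | implied yes | not applicable |

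The formal criteria, the consent procedure and the replacement procedure broadly agree. The 6.2 footnote departs from them for replacements, and 6.6 departs from them for every intervention resident.

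**3. How many residents could be affected.** Section 13.1.1 gives about 40% leaving or dying. Assume that 20% to 40% of places are refilled, once each. The share of replacements among all consented residents is s = L/(1 + L):

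- L = 0.2: s = 0.2/1.2 = 17%
- L = 0.4: s = 0.4/1.4 = 29%

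A constant-hazard version with immediate replacement up to 1 May (242 of 273 days) gives −ln(0.6) × 242/273 = 0.511 × 0.886 = 0.453 per place. In a home with 12 places that is 5.4 of 17.4 residents, or 31%. Replacement person-days are then at most 1 − 0.4/0.511 = 22%.

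Most of these people would have entered anyway. The protocol gives no refusal rate. If 10% to 30% of otherwise willing residents refused a filter (assumption), the residents actually swapped would be 31% × 10% to 30% = 3% to 9% of individuals, or 22% × 10% to 30% = about 2% to 7% of person-days.

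**4. Effect on the intervention-arm rate.** Let a be filter acceptance without the condition, and let every replacement accept. The acceptor share becomes A = (1 − s)a + s. If acceptors have q times the infection rate of decliners, the rate shifts by [Aq + (1 − A)] / [aq + (1 − a)]. Both a and q are assumptions. For L = 0.4:

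| a | A | q = 0.8 | q = 1.25 |
|---|---|---|---|
| 60% | 71% | 0.974 | 1.025 |
| 80% | 86% | 0.986 | 1.012 |
| 90% | 93% | 0.993 | 1.006 |
| 100% | 100% | 1.000 | 1.000 |

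For L = 0.2 the widest pair (a = 60%) is 0.985 and 1.014. At the extreme, a true rate ratio of 0.5 would be estimated as 0.5 × 0.974 = 0.487 or 0.5 × 1.025 = 0.513. The formula weights people equally, and replacements contribute fewer days, so it tends to overstate the shift. It covers underlying risk only, not the extra bedroom-filter coverage that more acceptors would bring.

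**The case against.** The strongest reply is that one footnote, attached to a flow chart that cannot be seen in the available text, should not outweigh the formal criteria and the operative procedure. The footnote says eligible if, not only if, and it can be read as asking whether a resident minds a used shell with a fresh filter. Sections 5.4.1, 6.5 and 6.15.2 already describe an offer. This stands in part: the defect is confined to the footnote and 6.6. But the footnote is worded as eligibility, and nothing in the protocol says that the other text overrides it, so a site could reasonably apply it.

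The protocol also has safeguards. Section 6.17 plans sensitivity analyses of continual recruitment, including a check for post-randomisation recruitment bias. Section 13.1.1 openly accepts unblinded recruitment of some participants in return for power. Section 13.1.2 repeats the analyses on anonymous data, whose residents are randomly selected without individual consent (6.7, 7.1), so filter acceptance cannot govern entry there. Consent already follows allocation, with arm-specific information sheets (7.2). The footnote therefore adds to an acknowledged risk. These analyses may reveal a difference, but they do not remove an arm-specific criterion from the primary analysis, and accepting unblinded recruitment is not the same as accepting different criteria by arm.

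A reader might infer that the intervention set is progressively enriched for filter acceptors, or that replacements face a condition which initial residents certainly do not. The documents do not support either. Enrichment requires sites to apply the footnote and some otherwise willing residents to refuse a filter, and the protocol reports neither. The contrast with initial residents follows from 5.4.1 and the and/or wording, but 6.6 points the other way. If 6.6 governed, initial and replacement residents would be treated alike, and the difference would lie between the arms from the start.

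**Conclusion.** The contradiction is real. The 6.2 footnote sets an eligibility condition that the criteria for consented residents do not contain, that 6.15.2 turns into an offer, and that can operate in one arm only. Section 6.6 is inconsistent with the and/or wording as well. If the footnote is followed, entry to the primary set after randomisation differs by arm, which is a possible selection bias.

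Its size is probably modest: at most about 2.5% either way on the intervention-arm rate. That rests on 40% of places being refilled once, 60% filter acceptance without the condition, and acceptors' rates 20% lower or 25% higher than decliners'. A stronger link between acceptance and infection would enlarge it. The direction is unknown, and the effect is nil if all otherwise willing residents accept a filter. The point does not threaten the trial's main conclusion, but it merits correction because the remedy is simple and closes a route to bias.

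**What to change.** - In the 6.2 footnote, delete the clause "if willing to accept same units with new air filters" together with the conjunction before it.
- Reword 6.6 so that consented residents in intervention homes are offered a bedroom filter.
- State once, and refer to it from 6.2 and 6.15.2: *Replacement residents meet the same criteria as initial residents (5.4.1 and 5.4.2) in both arms. In intervention homes the bedroom filter is offered but not required, and a resident may consent to notes review only.*
- Record on the register which consents are for notes review only.
- For homes already recruited, state which rule sites applied. The current version is dated September 2024 and version 11.0 of September 2023 already deals with Winter 3, so new wording probably cannot change who was enrolled. Knowing the rule used is what lets the 6.17 sensitivity analyses be interpreted.

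The cost is a short amendment and a query to sites or to the study team's own records. For any recruitment still to come, a few bedroom units may stand unused, which would slightly lower bedroom-filter coverage.
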